### Intervention

Included patients will undergo lung POCUS examination as part of their preoperative medical assessment prior to surgery. This is typically performed by an internal medicine specialist, and is usually done in a week to a few days in an outpatient clinic (in case of elective surgeries), and inpatient 0-1 days prior (in case of urgent surgeries). The studies will be performed by a sole operator (author LP), who was trained in POCUS during his internal medicine residency program, has attended POCUS courses via the American College of Physicians, and has been using POCUS on a daily basis in his clinical practice for more than five years. A single operator was chosen to eliminate the impact of inter-operator variability. POCUS images will be saved. To validate the findings, the operator's interpretation will be confirmed by an independent reviewer, who is a POCUS-trained critical care attending physician at NYC H+H/Jacobi (author PG). Clinicians will be blinded to lung POCUS findings, which is in-line with the high-quality POCUS literature [18]. Exceptions will include POCUS findings that are considered by the operator as critical, such as possible lung collapse, severe pulmonary edema, or large pericardial effusion, which will be reported to the clinicians.

A commercial handheld device will be used on its lung preset. The 12-zone lung POCUS examination will be performed (Figure 1). The iLUS will be calculated for every patient. The external lung fields will be examined dividing the surface of the thorax into 12 zones: 6 on the right (anterior: upper R1 and lower R2; lateral: upper R3 and lower R4; posterior: upper R5 and lower R6) and 6 on the left side (anterior: upper L1 and lower L2; lateral: upper L3 and lower L4; posterior: upper L5 and lower L6) (Figure 1). iLUS assigns 0 points to A-lines or?<2 separate B-lines plus regular sliding; 1 point with B-lines?≥3 or spaced focal points plus regular sliding; 2 points with coalescing B-lines, and 3 points to pulmonary consolidations with a score ranging from 0 (normal lungs) to 36 (worst case scenario). iLUS evaluation then integrates four additional parameters: i) presence of pleural effusion (value 0 if absent, value 1 if present), ii) presence of pericardial effusions (value 0 absent, value 1 present), iii) measurement of the inferior vena cava (IVC) respiratory variation (<33%) (value 0 if absent, value 1 if present), iv) diaphragm excursion. This last parameter will be measured during normal breathing via a right subcostal scan. An excursion?>2?±?0.5 cm will be considered normal (value 0 if absent), while a value below will be abnormal (value 1 if present). Therefore, the total value of the iLUS will be 40 (Table 3) [15].

**Figure 1. F1:**
[figure not shown]
The six chest areas per side considered for complete 12-zone lung POCUS examination. Areas 1 and 2 denote the upper anterior and lower anterior chest areas, respectively. Areas 3 and 4 denote the upper lateral and basal lateral chest areas, respectively. Areas 5 and 6 denote the upper posterior and lower posterior chest areas, respectively [31].

**Table 3. T3:** Integrated Lung Ultrasound Scoring (iLUS) system

Finding	Points
A0. A-line pattern or <2 B-lines with normal lung sliding	0
A1. ≥3 well-spaced B-lines	1
A2. Coalescing B-lines	2
A3. Pulmonary consolidation	3
B. Present pleural effusion	1
C. Present pericardial effusion	1
D. IVC variation <33%	1
E. Diaphragm excursion <2?±?0.5 cm	1

### Primary and Secondary Endpoints

The primary endpoint will be the composite of failure of extubation after surgery completion in the operation room with the need for re-intubation, unplanned use of continuous positive airway pressure (CPAP), bilevel positive airway pressure (BiPAP), or high-flow nasal cannula (HFNC) after postoperative extubation, admission to the intensive care unit for a primary cardiopulmonary etiology in the index admission, death from a primary cardiopulmonary etiology within 30 days from operation, or readmission for a primary cardiopulmonary etiology within 30 days from operation (whichever happens first). The secondary endpoints will be the individual components of the primary endpoint as above, the length of stay for patients discharged alive, the need for supplemental oxygen on post-operation day 1 in the surgery floor and the need for additional diagnostic tests or other interventions prior to the planned surgery as a response to critical POCUS findings. Length of stay is defined as the number of days from the day of the operation to the day when the patient is declared medically appropriate for discharge by the primary team.

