## Abstract

Abdominal surgeries make up a significant portion of all surgical procedures performed worldwide. Despite advances in surgical techniques, there is significant morbidity and mortality associated with abdominal surgeries. Cardiopulmonary complications in the postoperative period play an important part in the elevated risk associated with these surgeries. Preoperative medical assessments have therefore become the standard of care to evaluate the risk of surgery, optimize a patient's medical conditions, and mitigate the perioperative risk. While there has been increasing utilization of lung point of care ultrasound (POCUS) in the immediate preoperative setting, the use of lung POCUS at the preoperative medical assessment clinic visit has not been studied. While using risk stratification tools is common in current practice, the role of adjunctive office-based techniques like lung POCUS have not been studied in this setting. We conducted an observational prospective pilot study to evaluate the association of lung POCUS findings in the preoperative visit on the risk of adverse cardiopulmonary outcomes in the 30-day postoperative period after major abdominal surgery. A standardized scoring system called integrated lung ultrasound score (iLUS) is used for objective assessment. Our study attempted to determine whether the addition of lung POCUS can be used to better stratify the risk for postoperative complications.

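### The ICU component of the primary endpoint states no postoperative start, so a preoperative ICU admission, including one prompted by the scan, could be coded as a primary event

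*Protocol article*

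**What the plan says.** All references are to the protocol article. *Primary and Secondary Endpoints* defines a composite of five components, counted by whichever comes first. Four have an explicit postoperative anchor:

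- "failure of extubation after surgery completion in the operation room with the need for re-intubation"
- unplanned CPAP, BiPAP "or high-flow nasal cannula (HFNC) after postoperative extubation"
- "death from a primary cardiopulmonary etiology within 30 days from operation"
- "readmission for a primary cardiopulmonary etiology within 30 days from operation (whichever happens first"

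The fifth is "admission to the intensive care unit for a primary cardiopulmonary etiology in the index admission". Its only time bound is the hospital stay. The individual components are also secondary endpoints, so the same wording carries over to them.

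Other sections bear on how this is read:

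- *Intervention*: the scan is done "inpatient 0-1 days prior (in case of urgent surgeries". Critical findings are an exception to blinding, with examples including "severe pulmonary edema, or large pericardial effusion, which will be reported to the clinicians".
- *Methodology of Analysis*: patients whose critical findings lead to an intervention, postponement or cancellation stay in the primary analysis. A subgroup analysis of patients with critical findings and a sensitivity analysis without them are also planned.
- *Abstract*: the objective concerns "adverse cardiopulmonary outcomes in the 30-day postoperative period after major abdominal surgery". *Aims and Hypothesis* also speaks of postoperative outcomes, and *Participant follow-up and study duration* starts the 30 days on the day of surgery.

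**The concern.** For an urgent inpatient the index admission begins before the operation and may begin before the scan. Applied as written, the ICU component can therefore be met by an ICU admission that is not a postoperative outcome.

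The serious case is circular. A scan shows a critical finding, the clinicians are told, and the patient goes to the ICU before surgery. Critical findings such as severe pulmonary edema would be expected to go with a high iLUS. The index test would then help produce the event, in the group where the hypothesis predicts events. If the operation is then cancelled, the other four components have no operation or extubation to start from, so the ICU component is the only one the patient can clearly meet.

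At stake is an association between iLUS and the primary endpoint that is partly built in by the definition, in a study of only 120 patients where a handful of events can move the result.

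**Working it through.** **Step 1. Compare the time anchors.**

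| Component | Start stated in the article |
|---|---|
| Failed extubation | end of surgery |
| CPAP, BiPAP or HFNC | postoperative extubation |
| ICU admission | none; index admission only |
| Death | operation, to 30 days |
| Readmission | operation, to 30 days |

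The same section starts length of stay on the day of the operation, so the authors set that start elsewhere when they wanted it.

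**Step 2. Can preoperative time fall inside the index admission?** Yes, for urgent patients, who are scanned as inpatients 0–1 days before surgery. The planned analyses by emergent versus elective surgery show that non-elective patients are expected.

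**Step 3. Does a planned analysis remove the scan-triggered case?** The sensitivity analysis without critical findings does. The primary analysis does not, because it retains these patients.

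**Step 4. How large could the effect be?** The article states no event rate, effect size or power for N = 120, so there is no figure to reproduce. What follows is an illustration on assumed inputs:

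- 60 patients in each iLUS group (120/2, roughly a median split);
- true postoperative risk b of 10%, 15% or 20%, equal in both groups;
- a probability e of a counted preoperative ICU stay, in the high-iLUS group only unless stated.

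Observed risk with such stays = 1 − (1 − b)(1 − e). For b = 0.15:

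- e = 0.05 (3 of 60 expected): 1 − 0.85 × 0.95 = 0.1925, and 0.1925/0.15 = RR 1.28
- e = 0.10 (6 of 60 expected): 1 − 0.85 × 0.90 = 0.235, and 0.235/0.15 = RR 1.57

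The chance of p ≤ 0.05 comes from summing exact binomial probabilities over all outcomes, using a two-sided pooled z test:

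| Preoperative ICU stays counted | b = 10% | b = 15% | b = 20% |
|---|---|---|---|
| none | 5.0% | 4.7% | 5.0% |
| one expected, high iLUS (e = 1/60) | 5.8% | 5.2% | 5.4% |
| six expected, split 4 high : 2 low | 7.1% | 6.7% | 6.6% |
| e = 5%, high iLUS only | 11.2% | 9.0% | 8.4% |
| e = 10%, high iLUS only | 27.9% | 21.6% | 18.0% |

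The article does not fix the test. Fisher's exact test gives 5.2–6.8% at e = 5% and 12–21% at e = 10%, against 2.2–2.8% with no such stays.

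**The case against.** The best case against the point is that the article's intent is plainly postoperative. The objective, the aims and the follow-up section all say so, and follow-up begins on the day of surgery. In the list of components, the reference to the index admission reads naturally as separating an ICU admission before discharge from the readmission that follows. Preoperative interventions prompted by critical findings already have their own secondary endpoint. The planned subgroup and sensitivity analyses would bring a scan-triggered effect to light. The study is an observational pilot, and the large figures above need both a high rate of such stays and their complete concentration in the high-iLUS group.

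Most of this stands, and it rules out two stronger readings. A reader might infer that preoperative ICU stays do count as primary events. The article never says that; it only fails to exclude them. A reader might also infer that an ICU stay before the scan is an equal threat. It is a weak example, because it precedes both the scan and the start of follow-up.

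The objection does not dispose of the point. Evidence of intent elsewhere makes the wording inconsistent with the rest of the article; it does not supply the missing start. The follow-up section sets a duration and does not define the ICU event. The secondary endpoint for preoperative responses neither names ICU admission nor removes it from the composite. The sensitivity analysis would expose the problem but leaves the primary result as it is. Nor is this a detail left to a fuller document: the article states the component, and states its bound badly.

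**Conclusion.** The point holds as a defect in the stated definition. The ICU component alone lacks a postoperative start, which is inconsistent with the stated objective and follow-up. Together with the reporting of critical findings and the retention of patients whose surgery is postponed or cancelled, it leaves room for the scan to contribute to its own endpoint.

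The size of any bias is unknown. The article gives no event rate, no share of urgent surgery and no preoperative ICU rate. On the assumed inputs, the false-positive rate is near nominal with one such patient expected (5.2–5.8%), 6.6–7.1% if six are split 4:2, and 18–28% in the extreme case of a 10% rate confined to the high-iLUS group. These figures show sensitivity at N = 120 and do not predict what will happen.

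**What to change.** 1. Define the ICU component, and the matching secondary endpoint, as an ICU admission for a primary cardiopulmonary etiology that begins after the operation, in line with the Abstract and the follow-up section.
2. Record preoperative ICU stays separately: as a baseline characteristic if before the scan, and under the existing secondary endpoint for preoperative responses if prompted by the scan.
3. State how patients whose surgery is cancelled are counted in the primary analysis, since they have no operation date from which to start the postoperative windows.

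The cost is one phrase in the endpoint definition, one field on the case report form and a sentence in the analysis section. The downside is slightly fewer primary events. The change should be made before outcomes are coded, so that no ruling on individual primary events is needed afterwards.

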### Participant follow-up and study duration

Participants will be followed for 30 days from the day of surgery. Postoperative complications after laparotomy are most common within a median of 9 days after surgery. Therefore, a follow up period of 30 days ensures that all acute cardiopulmonary complications are included [20]. The study is expected to be completed within two years after its initiation. The patient flow from intake into the study until completion of the study is demonstrated in Figure 2.

**Figure 2. F2:**
[figure not shown]
Process flowchart of the study

### Safety, Adverse Events Definition, and Reporting

Ultrasound imaging has been used for over 30 years and has an excellent safety record. It is based on non-ionizing radiation, so it does not have the same risks as X-rays or other types of imaging systems that use ionizing radiation [21]. POCUS has become standard practice in various aspects of daily clinical practice [22]. No adverse events are expected from POCUS, and this study poses no more than minimal risk for the included patients. POCUS findings that are considered by the operator as critical, such as possible lung collapse, severe pulmonary edema, or large pericardial effusion, will be reported to the primary team.

### Methodology of Analysis

The following 3 classifications of patients will be performed based on the iLUS: i) iLUS 0 vs. >0, ii) iLUS < mean iLUS vs. ≥ mean iLUS, iii) iLUS < median iLUS vs. ≥ median iLUS.

Continuous variables will be presented as mean with standard deviation and median with interquartile range. Categorical variables will be presented in absolute and relative frequencies. The appropriate parametric and non-parametric tests will be utilized for generating comparisons.

A sensitivity analysis will be performed for patients enrolled in the Jacobi site and patients enrolled in the Laikon site. Sensitivity analyses will be performed for various patient groups based on RCRI, ASA-PS, and AUB-HAS-2 scores, as well as whether the surgery was emergent or elective as deemed by the primary surgical team [23].

Multivariate analysis will be performed including iLUS classification and the following variables: age, sex, body mass index (BMI), RCRI, ASA-PS, and AUB-HAS-2 scores, time from POCUS scan to surgery, and emergent vs. elective surgery.

In addition, to preserve the integrity of our analysis while still reporting critical lung POCUS results, we will implement the following analysis: All patients enrolled in the study will be included in the primary analysis based on the intention-to-treat (ITT) principle to ensure that our results will reflect real-world practices. Patients with critical POCUS findings prompting interventions, postponement, or cancellation of surgery will be retained in the ITT analysis to maintain randomization integrity. Additionally, a pre-specified subgroup analysis will focus exclusively on these patients to evaluate the specific impact of the critical POCUS results on outcomes such as completion of surgery, postoperative complications, intensive care unit admission, mortality, length of stay, and readmissions. To further assess the robustness of our findings, a sensitivity analysis will be conducted, excluding patients with critical findings to evaluate the effect of blinding on the study outcomes.

An interim analysis will be performed after the follow-up completion of 60 participants (with at least 10 participants at the Laikon site). Should the interim analysis reveal findings that decisively confirm or reject the study hypothesis, no more participants will be enrolled, and the study will be ended after the follow-up completion of the last enrolled participant.

The statistical significance threshold will be set at p ≤0.05. Analysis will be conducted with STATA software (version 14.1, STATA corporation, College Station, TX, USA).

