### Population, Inclusion and Exclusion Criteria

We plan to include 120 men and women (at least 20 of them from the Laikon site) with the inclusion criteria consisting of patients ≥50 years of age, who undergo preoperative medical assessment for a major abdominal surgery under general anesthesia, have RCRI ≥2 (moderate or higher risk), and ASA-PS: II, III, IV (Table 1 and 2).

**Table 1. T1:** Revised Cardiac Risk Index (RCRI) for preoperative risk

RCRI clinical variable	Points
Elevated-risk surgery (intraperitoneal, intrathoracic, suprainguinal vascular)	1
History of ischemic heart disease	1
History of congenital heart failure	1
History of cerebrovascular disease	1
Preoperative treatment with insulin	1
Preoperative creatinine >2 mg/dL	1

**Table 2. T2:** American Society of Anesthesiologist's Physical Status (ASA-PS) - ASA classification

ASA Classification	Definition
ASA I	Normal healthy patient
ASA II	Patient with mild systemic disease
ASA III	Patient with severe systemic disease
ASA IV	Patient with severe systemic disease that is constant threat to life
ASA V	Moribund patient not expected to survive without operation
ASA VI	Declared brain dead patient whose organs are being removed for donor purposes

The exclusion criteria will be age <50 years, surgery other than major abdominal, anesthesia other than general, RCRI <2 points, and ASA-PS other than 2, 3, or 4.

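### iLUS is analysed as three two-group splits, two cut at the sample's own mean and median, and none is named as the lead exposure although a stopping decision depends on the result

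*Protocol article*

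**What the plan says.** All places are in the protocol article.

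- **Score (Intervention).** Twelve zones are graded 0 to 3 and four yes/no findings are added: "Therefore, the total value of the iLUS will be 40". The score takes whole-number values.
- **Exposure (Methodology of Analysis).** "The following 3 classifications of patients will be performed based on the iLUS: i) iLUS 0 vs. >0", followed by "ii) iLUS < mean iLUS vs. ≥ mean iLUS, iii) iLUS < median iLUS vs. ≥ median iLUS". No order of importance is given.
- **Adjusted model (same section).** "Multivariate analysis will be performed including iLUS classification and the following variables". The noun is singular and the text does not say which of the three is meant. No model of the uncut score is described.
- **Threshold (same section).** "The statistical significance threshold will be set at p ≤0.05".
- **Size and interim look.** "We plan to include 120 men and women" (Population, Inclusion and Exclusion Criteria) and "An interim analysis will be performed after the follow-up completion of 60 participants" (Methodology of Analysis). Enrolment ends early if the interim findings settle the hypothesis either way.

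**The concern.** With three unranked versions of the exposure, the study has three routes to a significant result. At the interim look, nothing says which version decides whether enrolment stops.

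Two of the cuts are statistics of the sample. A patient can change group between 60 and 120 patients without any change in that patient's score. A cut at this cohort's mean or median also has no meaning in another cohort, yet the Conclusion offers the results as a basis for larger randomised trials.

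The median and mean rules can also break down on a whole-number score with many zeros, and two-group coding gives up information if risk rises steadily with the score.

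**Working it through.** The article gives no effect size, event rate or power for the 120 patients, so there is no design figure to reproduce. The stated inputs are N = 120, interim N = 60, p ≤0.05 per test (two-sided assumed) and a score of 0 to 40. Two inputs are assumptions: the composite event rate (10%, 20% and 30%, inside the 9 to 40% that the Introduction quotes for pulmonary complications) and the iLUS distribution (right-skewed, with 4% to 60% of patients at 0).

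**1. False positives across three splits.**
- If the tests were independent: 1 − (1 − 0.05)³ = 1 − 0.857 = 14.3%. This is only a reference, because the three splits cut the same score and are correlated.
- Simulation under no association (2,500 datasets per scenario, pooled two-proportion z test on each split, counting any p ≤0.05): 6.4% to 12.6% at N = 120.
- At N = 120 and 30% events, by share of zeros: 12.6% (4% zeros), 11.9% (20%), 11.0% (30%), 8.8% (40%), 8.3% (50%), 6.9% (60%). The excess shrinks as zeros increase because splits then coincide or disappear.
- These figures leave out the interim look, the subgroups and the secondary endpoints.

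**2. When the below-median group is empty.** With 120 patients the median is the average of the 60th and 61st ordered scores. It equals 0 exactly when at least 61 patients score 0, and then nobody lies below it. With p₀ the probability of scoring 0, P(median = 0) = P(Binomial(120, p₀) ≥ 61).

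| p₀ | P(below-median group empty), N = 120 |
|---|---|
| 60% | 98% |
| 55% | 84% |
| 50% | 46% |
| 45% | 12% |
| 40% | 1% |
| 35% | 0.03% |

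**3. When splits coincide.** On a whole-number score, a cut c with 0 < c ≤ 1 puts exactly the zeros below it, so that split is the same as 0 vs >0. In simulation at N = 120 and 20% or 30% events, the median split duplicated 0 vs >0 in about 82-83% of datasets with 40% zeros and about 26% with 30% zeros. The mean split did so in about 52-55% under a low-mean distribution (54% zeros). With 20% zeros or fewer these failures are rare. The mean split cannot be empty unless all scores are equal.

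**4. Power if log-odds are linear in the score** (N = 120, 20% events).

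| Odds ratio per SD | Uncut score | Mean split | Median split | 0 vs >0 |
|---|---|---|---|---|
| 1.6 | 62-66% | 41-43% | about 5-32% (both splits together) | as left |
| 1.82 | 79-85% | 57-64% | 1-47% | 1-49% |

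The lowest median-split value comes from scenarios where the group is usually empty. The lowest 0 vs >0 value comes from the scenario with only 4% zeros. The share of information kept, measured as the squared correlation of split and score, is 56-60% for the mean split, 35-55% for a non-empty median split and 7-45% for 0 vs >0.

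**5. Power if risk steps instead.**
- Step at 0 (5% vs 28% risk, 35% zeros): 0 vs >0 has 92% and the uncut score 46%. A separate simulation of a step at 0 with 35% zeros gave 91% and 43%.
- Step at the median (10% vs 30%): the median split has 73-75% and the uncut score 45-47%.

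The ranking of the methods therefore depends on the shape of the relation, which the article does not state.

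**The case against.** The strongest reply has four parts.

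- **Pilot status.** This is an observational pilot. All three rules are written down in advance, and the mean and median rules do not look at outcomes, so this is not a search for the best cut. That stands and lowers the severity. It does not explain why a significance threshold and a stopping decision rest on an unranked set.
- **Unseen documents.** A full protocol or SAP could name the lead split, handle empty groups or adjust for multiplicity. That is fair, and silence alone would not make this a point. However, the article itself fixes the sample-derived cuts and puts a classification in the adjusted model, and a SAP that only ranked the splits would leave both in place. The general sentence on parametric and non-parametric tests could allow a comparison of uncut scores, but it does not name iLUS.
- **Empty splits are hypothetical.** A reader might infer that the median split will fail. The article gives no iLUS distribution, and a score of 0 needs twelve normal zones and none of four extra findings in patients aged 50 or over with RCRI ≥2. A majority at 0 is possible but unsupported. An empty or duplicated split also adds no false positive, so the worst cases in steps 1 and 2 do not occur together.
- **Power.** A reader might infer that two-group coding must cost much power here. Step 5 shows that this can reverse under a threshold effect. Since iLUS adds zone grades to four yes/no findings, linearity per point is not self-evident.

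**Conclusion.** The point holds in a limited form and should be fixed; it does not invalidate the study.

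**Firm, from the text alone:** three unranked splits, two cut-points taken from the sample, an adjusted model that does not say which split it uses, and an interim decision with no named exposure. The sample cuts can shift between looks and cannot be transferred.

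**Conditional on assumed distributions:** a false-positive chance of about 6-13% at N = 120, which is at most about 2.5 times the nominal level (12.6 / 5) and below the 14.3% that independence would give. An empty median split is a material risk only with about half or more of patients at 0.

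**Conditional on shape:** the power loss applies if risk rises roughly linearly with iLUS. It is not a general property of the plan.

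**What to change.** Before outcome data are analysed, state one primary exposure: iLUS as a continuous score in a logistic regression of the composite endpoint, reported per point or per SD, with a pre-specified spline check of linearity. Use the same term in the adjusted model, and name it as the exposure on which the interim decision rests. Keep iLUS 0 vs >0 as the single pre-specified secondary split. Drop the mean and median splits, or label them exploratory with no claim attached.

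A single primary exposure, tested once, brings the error at the final analysis back to 5%, before any allowance for the interim look. If three co-primary splits were kept instead, a Bonferroni threshold would be 0.05 / 3 = 0.0167 each, and the cuts would still be sample-derived.

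The cost is wording only, with no new data and no change to scanning. There are two downsides. A per-point odds ratio is harder to read than a two-group table, and the continuous test loses power if the true effect is a threshold at 0. The retained 0 vs >0 split supplies the table and would show such a threshold.

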Cardiovascular complications, mainly myocardial ischemia, left ventricular dysfunction, and arrhythmia—occur in one in seven patients older than 45 years within 30 days from an inpatient non-cardiac surgery [6]. Similarly, pulmonary complications are common—particularly after major abdominal surgery—with an estimated incidence of 9 to 40%. Atelectasis, pneumonia, and pulmonary aspiration are among the most common postoperative complications and can impact survival after surgery. Preoperative medical assessment prior to every major surgery has become the standard of care with objectives to assess the perioperative risk for morbidity and mortality, optimize the patient's medical condition, and mitigate the risk for cardiopulmonary complications and others [9]. A number of validated risk stratification tools, such as the Revised Cardiac Risk Index (RCRI), American University of Beirut (AUB)-HAS2 Cardiovascular Risk Index, the American Society of Anesthesiologist's Physical Status (ASA-PS), and the Gupta perioperative risk for myocardial infarction and cardiac arrest have been created and used to standardize and optimize the perioperative medical assessment process [10–12]. The utilization of point of care ultrasound (POCUS)—the application of portable ultrasound by clinicians at the bedside—has grown rapidly in the inpatient and outpatient settings and is a valuable tool that enhances the standard clinical assessment [13]. In particular, lung POCUS can reveal findings, such as mild pulmonary edema, atelectasis, fibrosis, or small pleural effusions, which can be subclinical and otherwise not detected by history and physical examination alone [14]. A structured approach to performing and evaluating lung POCUS has been highly useful. This was originally known as the lung ultrasound score, and was later refined by Dell'Aquila et al. as the integrated lung ultrasound score (iLUS) [15,16].

Studies conducted in the immediate preoperative period have shown that lung POCUS performed during anesthesiology evaluation can aid in determining fluid therapy and predicting major adverse cardiac events [17,18]. However, the specific role of POCUS beyond this immediate preoperative assessment of patients has not been studied adequately, especially in the clinic setting at the time of preoperative medical assessment [19].

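### The adjusted iLUS model has no lung-specific baseline covariate, so the study could not show that the scan adds to a known pulmonary history

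*Protocol article*

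**What the plan says.** All references are to the protocol article.

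- **Adjusted model.** Methodology of Analysis gives the covariates by name. They are the iLUS class plus "age, sex, body mass index (BMI), RCRI, ASA-PS, and AUB-HAS-2 scores, time from POCUS scan to surgery, and emergent vs. elective surgery".
- **Sensitivity groups.** The same section lists site, RCRI, ASA-PS, AUB-HAS-2 and urgency, and an analysis without patients who had critical findings.
- **Nature of the scores.** The Introduction lists among the established tools "the Revised Cardiac Risk Index (RCRI), American University of Beirut (AUB)-HAS2 Cardiovascular Risk Index". Table 1 gives six RCRI items, for example "History of ischemic heart disease", and none is pulmonary. Table 2 defines ASA-PS by overall disease severity, for example "Patient with severe systemic disease".
- **Eligibility.** The exclusions are "age <50 years, surgery other than major abdominal, anesthesia other than general, RCRI <2 points, and ASA-PS other than 2, 3, or 4". Known lung disease is not among them.
- **Endpoint.** Two of the five components in Primary and Secondary Endpoints are purely respiratory: failed extubation with re-intubation, and "unplanned use of continuous positive airway pressure (CPAP), bilevel positive airway pressure (BiPAP), or high-flow nasal cannula (HFNC) after postoperative extubation". The other three are ICU admission, death and readmission, each for a cardiopulmonary cause, for example "admission to the intensive care unit for a primary cardiopulmonary etiology in the index admission".
- **Rationale.** The Introduction supports lung POCUS by findings "which can be subclinical and otherwise not detected by history and physical examination alone". The Abstract asks whether adding it improves risk stratification.

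**The concern.** Known chronic lung disease may both raise the iLUS and make postoperative respiratory support more likely. The Introduction itself counts fibrosis among the things lung POCUS can show. If that link exists and the model does not hold lung disease fixed, part of the adjusted iLUS association is information that the internist already had from the history.

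This bears on the study's own question. To show that a test adds to the usual assessment, the comparison model must contain what that assessment already knows. Here the model carries two cardiac or cardiovascular indices and nothing specific to the lung. A positive result would therefore leave open whether the scan found something new or recorded known disease. The Conclusion intends the results to inform randomized trials and eventually guidelines, so this ambiguity would carry forward.

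The covariates and sensitivity groups are named in the article. Their content is a stated choice, not a detail left to an unseen analysis plan.

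**Working it through.** The article states no power, effect size or expected event count, so there is no figure to reproduce. I made three checks.

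**1. Does any listed variable measure the lung?**

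| Variable | Content according to the article |
|---|---|
| Age, sex, BMI | demographic and body size |
| RCRI | six items in Table 1, none pulmonary |
| AUB-HAS-2 | named a cardiovascular index; its items are not listed |
| ASA-PS | global grade; three levels can enter (II, III, IV) |
| Scan-to-surgery time, urgency | logistics and acuity |

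None is lung-specific. On the exposure side, 12 zones × 3 points = 36 of the 40 iLUS points come from B-lines and consolidation. Pleural effusion and diaphragm excursion add 2 more. Pericardial effusion and IVC variation, which are not lung findings, make up the last 2.

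**2. How large could the effect be?** The article gives no prevalence of lung disease and no associations, so every input here is an assumption except N = 120 and the 9–40% range. That range is the Introduction's incidence of pulmonary complications, borrowed here as an event rate. In all cases iLUS has no effect once lung disease is known.

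*One case by hand.* Assume lung disease in 20% of patients, 80% of them at or above the iLUS median, a 15% event risk without lung disease, and an odds ratio of 3 for the endpoint.
- Share with high iLUS among the others: (0.50 − 0.20 × 0.80) / 0.80 = 0.425.
- Event risk with lung disease: odds 3 × 0.15/0.85 = 0.529, so risk 0.529/1.529 = 0.346.
- Risk with high iLUS: (0.20 × 0.80 × 0.346 + 0.80 × 0.425 × 0.15) / 0.50 = 0.213.
- Risk with low iLUS: (0.20 × 0.20 × 0.346 + 0.80 × 0.575 × 0.15) / 0.50 = 0.166.
- Apparent odds ratio: (0.213/0.787) / (0.166/0.834) = 1.36.

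*Range.* Lung disease in 15% or 30% of patients, a 50/50 iLUS split, and event rates of 9%, 20% and 40%. The logistic intercepts were solved to match these margins. The odds ratio comes from the 2×2 table collapsed over lung disease, and the rejection rate from simulated two-sided 5% Pearson chi-square tests.

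| Odds ratio of lung disease with high iLUS / with endpoint | Apparent iLUS odds ratio | Rejection rate |
|---|---|---|
| 1 / 1 (check) | 1.00 | about 5% |
| 2 / 2 | 1.06–1.12 | 5–6% |
| 3 / 3 | 1.16–1.32 | 6–10% |
| 5 / 3 | 1.22–1.47 | 7–15% |
| 5 / 5 | 1.33–1.78 | 10–27% |

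These figures are **before any adjustment**. They are not results of the planned multivariate model. In the setup above, holding lung disease fixed returns the iLUS odds ratio to 1.0.

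**3. Can the model carry another term?** The iLUS class plus eight covariates is at least nine parameters, counting each score as one term.
- At a 9% event rate: 120 × 0.09 = 10.8 events, or 10.8/9 = 1.2 per parameter. With one more term, 10.8/10 = 1.1.
- At 40%: 120 × 0.40 = 48 events, or 48/9 = 5.3 per parameter. With one more term, 48/10 = 4.8.

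The model is already heavily loaded. One yes/no term makes it slightly worse.

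**The case against.** The strongest reply is that the covariates fit the stated comparator. The Abstract and Introduction set lung POCUS beside the risk tools in use, and the model adjusts for three of those named: RCRI, AUB-HAS-2 and ASA-PS. For a question of association or stratification, an iLUS that carries information on lung disease is not wrong in itself. This stands as a defence of the listed model, and it is a reason not to drop either cardiac index. It does not reach the further claim that the scan shows what the history misses, because that needs the history in the model.

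Several other points also stand:
- The link between known lung disease in general and a high iLUS is assumed. Fibrosis is the only clearly chronic lung finding that the article ties to lung POCUS, and Table 3 gives an A-line pattern no points.
- The odds ratios of 2–5 have no source in the article, and the figures come from an unadjusted test. ASA-PS in particular would absorb some of the effect.
- That AUB-HAS-2 lacks lung content is inferred from its name.
- This is a small pilot with few events, so which covariates to spend them on is partly a judgement.

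A reader might go further and infer that the endpoint is mainly respiratory and that any iLUS effect would simply be known lung disease. The documents do not support that. Only two of five components are purely respiratory, the iLUS also scores pericardial effusion and IVC variation, and every patient has RCRI of at least 2, so cardiac adjustment is relevant.

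**Conclusion.** The point holds in a limited form. No covariate or sensitivity group named in Methodology of Analysis is specific to the lung, known lung disease is not excluded, and every component of the composite can be reached through lung disease. The planned analysis therefore cannot separate what iLUS adds from what the pulmonary history already tells.

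How much this matters is unknown. The illustration runs from negligible (odds ratio about 1.06, rejection about 5%) to moderate (about 1.78, and up to about 27%). It rests on assumed prevalences and associations, on no true iLUS effect, and on no capture by the listed covariates. Partial capture by ASA-PS would shrink it. The finding is that the design leaves the question open; it does not show that the iLUS result will be biased by any given amount.

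**What to change.** In Methodology of Analysis:

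1. Keep the listed covariates, and prespecify a supplementary adjusted model that adds known chronic lung disease (yes/no), taken from the history at the preoperative medical assessment. Report the iLUS estimate from both models side by side.
2. Add known lung disease (yes/no) to the listed sensitivity groups, so that the iLUS association is also shown in patients without it.

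The cost is a sentence or two in the plan, one more item abstracted from the history, and one more parameter in a model with few events (about 1.2 to 1.1 events per parameter at a 9% event rate, 5.3 to 4.8 at 40%). The supplementary estimate will be imprecise and should be read as such. RCRI and AUB-HAS-2 need not be removed, and no new procedure or patient is needed.
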